### Integrated cardiovascular risk reduction intervention (Aim 2)

A randomized controlled trial of families of individuals with a positive history of CHD will be used to address Aim 2 (Fig. 1). *Eligibility criteria*: Eligible families will include those with at least one family member with physician confirmed CHD diagnosed before the age of 55 years. If there are family members who have died from CHD (physician confirmed deaths) before the age of 55 years, such families will also be eligible to participate in the study. The medical records of CHD patients will be used to confirm the diagnosis and the age of the index case. A written informed consent to the study randomization plan from the head of the family will be a mandatory eligibility criterion. All participating family members will be required to provide individual consent to participate. *Family randomization*: Each family will be randomly assigned to participate in either the treatment intervention arm (integrated CVD risk management) or usual care arm (no interventions other than initial screening). Computer generated random numbers generated by an independent member who is not involved in the study will be used for randomization. Randomization of a family will be performed only after collection of complete baseline data. The outcome assessors and the data manager will be blinded from the intervention assignment. The data analysts will be provided with the intervention assignment only after complete database lock. *Participant eligibility criteria*: A minimum of two members from each family will be included even if they reside in separate houses. Potential participants must be more than 18 years of age and either first degree blood relatives or spouses of the index case. Bedridden and terminally ill patients will be excluded from the study. The detailed study flow chart is presented in Fig. 1. *Follow-up period:* All participants will be followed-up for two years after randomization. Study related measurements will be conducted at baseline, one year and two year time-points. The full study flow chart is presented in Fig. 2.

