#### Data collection

A structured questionnaire will be administered by trained staff to collect relevant data at baseline, one year and two year time-points. The questionnaire includes assessments of demographic and socio-economic variables, general health status, diet pattern, physical activity, tobacco, and alcohol consumption. The World Health Organization (WHO) STEPS instrument for chronic risk factor surveillance has been modified and adapted to capture local, contextual information [16]. Dietary data will be collected using a semi-quantitative food frequency questionnaire on food items that are relevant to chronic diseases and adapted from an ongoing cluster randomized trial in India [17]. Additionally, all participants will undergo anthropometric and BP measurements at three time points (baseline, year 1 and year 2). Anthropometric measurements include height (in cm), weight (in kg) and waist circumference (in Inches). BP and pulse rate will be measured using electronic BP monitors (OMRON HEM-7130-L) at all three time-points. Three measurements will be taken at the respective houses of the participants by trained staff, two minutes apart and after allowing the participant to relax for at least five minutes before starting the measurement. Participants will be instructed not to consume any beverages (coffee, tea or soft drinks) and alcohol at least one hour before taking the measurements. They will also be instructed to abstain from smoking. In fasting stage, 5 ml of blood will be collected at three time-points, centrifuged at source for serum and plasma separation, and transported to the study laboratory. They will be stored under −20 °C freezer. The following biochemical analyses will be performed on the collected blood samples: lipid profile (total cholesterol, LDL cholesterol, HDL cholesterol and VLDL cholesterol), fasting plasma glucose, and haemoglobin A1c (Table 2). Abstinence from tobacco at year 1 and year 2 will be validated by assessing urinary cotinine metabolites. Spot urine samples are collected at year 1 and year 2 for this purpose. The study laboratory is accredited by the National Accreditation Board for testing and calibration of Laboratories (NABL), India and also part of international external quality assurance programs (EQAS) such as EQAS of BIO-RAD.

**Table 2 Tab2:** Study measurements

Study parameters	Method/Instrument

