#### Study outcomes

To address Aim 2, several clinical outcomes are assessed. *Primary outcome*: proportions in each group achieving or improving risk factor control status (BP < 140/90 mmHg, fasting blood glucose (FPG) < 110 mg/dl, low-density lipoprotein (LDL) < 100 mg/dl, abstinence from smoking/tobacco use: at least 3 out of 4 risk factors). Secondary outcomes: 1) between group difference in number of optimal cardiovascular health indicators (BP < 120/80 mmHg, TC < 200 mg/dl, FPG < 100 mg/dl, >150 min/week of moderate intensity physical activity, BMI < 25 kg/m2, never used tobacco or quit >6 months ago and a healthy diet score) [18], 2) between group mean difference in main risk factors (SBP, DBP, LDL, FPG, and HbA1c), 3) proportions meeting >80% of recommended process measures (smoking cessation, moderate or high intensity physical activity, and <5 g per person/day salt consumption, >3 daily servings of fruits and vegetables, <2 table spoons/cubes of free sugar), and 4) proportions achieving or maintaining ten year Framingham cardiovascular disease (CVD) risk score [19]/WHO CVD risk score [20] of <10% or the INTERHEART non-laboratory based score of <5 [21].

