### Data analysis plan

All quantitative analyses (for Aim 2) will follow recommended intention to treat guidelines for RCT. A generalizing estimating equations (GEE) framework for clustered data [23] will be used to assess the statistical significance of any observed intervention effect on the primary endpoint. In this analysis, the dependent variable will be the indicator for whether the study participant is at three or more CVD risk factor reduction goals at the end of 12 and 24 months follow-up period, minus the observed probability of this endpoint in the absence of an intervention (rate in control group). An exchangeable working correlation matrix will be used to incorporate the clustering within the families, with a log link and binomial variance specified. The exponentiated point and interval estimates from the intercept of this model will quantify the intervention effect. A similar GEE approach will be used to estimate and test the significance of intervention effects on secondary endpoints. For continuous markers, such as SBP, FPG, HbA1c and LDL, the within-participant difference will serve as the dependent variable in a GEE model as above, with the identity link function and the distribution specified as normal. To assess the causal effect of the intervention adjusted for bias due to non-adherence and loss to follow up, marginal structural models will be fit, embedded around the analysis approaches outlined above [24].

All qualitative data, including that collected for Aim 1 and Aim 3, will comprise the verbatim transcripts of the audio recordings from all focus group discussions and interviews. Audiotapes of focus group discussions/interviews will be transcribed, de-identified, and the transcriptions audited for accuracy. Using ATLAS.ti software to manage the data, analyses of the textual data will follow the thematic analysis (e.g., for suggestions from patients and care givers for the intervention). Key themes will be identified from the data (inductively) and from the discussion guides (deductively), and these themes will be compared using structured comparisons to identify specific issues relevant to sub-groups of participants.

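### Neither the change-score analysis of the continuous markers nor the primary model adjusts for baseline, which loses precision and leaves the estimates sensitive to chance imbalance

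*Protocol article*

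**What the plan says.** All places are in the protocol article.

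- **Continuous markers (Data analysis plan).** For SBP, FPG, HbA1c and LDL, "the within-participant difference will serve as the dependent variable in a GEE model as above", with identity link and normal distribution. No covariate is named.
- **Primary outcome (Data analysis plan).** The dependent variable is "the indicator for whether the study participant is at three or more CVD risk factor reduction goals at the end of 12 and 24 months", less the rate observed in the control group. The model is set out thus: "An exchangeable working correlation matrix will be used to incorporate the clustering within the families, with a log link and binomial variance specified". The effect is taken from the intercept: "The exponentiated point and interval estimates from the intercept of this model will quantify the intervention effect". Neither an arm term nor a baseline term is described. The only adjustment mentioned is by marginal structural models, for non-adherence and loss to follow-up.
- **Baseline data (Integrated cardiovascular risk reduction intervention, Aim 2).** "Study related measurements will be conducted at baseline, one year and two year time-points", and "Randomization of a family will be performed only after collection of complete baseline data".
- **Tobacco verification (Data collection).** Cotinine is not measured at baseline: "Spot urine samples are collected at year 1 and year 2 for this purpose".
- **Primary outcome definition (Study outcomes).** It is worded as "proportions in each group achieving or improving risk factor control status". This implies a reference to baseline that the indicator in the analysis section does not carry.

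**The concern.** A change score subtracts the baseline value in full, which amounts to fixing its coefficient at 1. The best-fitting coefficient, with similar variances at both times, is the correlation r, which is below 1. The change score therefore over-corrects: if one arm starts worse by chance, part of its later improvement is regression to the mean. The primary model has the opposite weakness. It makes no use of baseline, so an arm that starts with more participants at goal tends to finish with more.

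At stake are confidence intervals wider than the same data would support, and estimates that can be questioned if a baseline table shows imbalance. Adjustment chosen at that point, after the allocation is known, is harder to defend than adjustment fixed beforehand.

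**Working it through.** **Inputs from the protocol article (Trial sample size and power).** 740 families, 370 per arm, at least two participants each; 45% against 55%; two-sided alpha 0.05; power 90%; ICC 0.20 for the composite primary outcome; 15% loss.

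**Assumed, because the document gives no figure.** Correlation r = 0.3 to 0.8 between baseline and follow-up for the continuous markers. Correlation φ = 0.3 to 0.5 between baseline and follow-up status on the composite. Equal variance at both times. ICC 0.20 is borrowed from the composite for the continuous markers, which have none of their own.

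**1. The plan's own figure.** The pooled two-proportion formula without continuity correction gives 524 per arm. The design effect is 1 + (2 − 1) × 0.20 = 1.2, and 524 × 1.2 = 628.8. Then 628.8 / 0.85 = 739.8, so 740 participants or 370 families per arm. In reverse, 740 × 0.85 / 1.2 = 524.2 effective per arm gives 90.0% power. The stated size is reproduced, as an unadjusted comparison.

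**2. Precision for continuous markers** (in units of σ²). The variance of a change is 2(1 − r). The baseline-adjusted variance is 1 − r². The ratio is (1 − r²) / [2(1 − r)] = (1 + r)/2. For an endpoint with 80% power on the change score, adjusted power is Φ[(1.96 + 0.84) × √(2/(1 + r)) − 1.96].

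| r (assumed) | Variance ratio, adjusted / change | Variance saved | Power, if 80% on change score |
|---|---|---|---|
| 0.3 | 0.65 | 35% | 93.5% |
| 0.5 | 0.75 | 25% | 89.9% |
| 0.7 | 0.85 | 15% | 86.0% |
| 0.8 | 0.90 | 10% | 84.0% |

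The difference detectable with 80% power is 2.80 × √(2 × variance / 524). At r = 0.5 the change-score variance is 1, giving 0.173 SD; the adjusted variance is 0.75, giving 0.150 SD.

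A simulation (3000 runs for each r, 315 families of two per arm, ICC 0.2, least-squares fits) gave ratios of 0.669, 0.766 and 0.863 at r = 0.3, 0.5 and 0.7, close to theory.

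**3. Is the change score biased?** In the same simulation, with a true effect of 0.10, its mean was 0.100, 0.102 and 0.100. It is unbiased over randomisations. Given a realised imbalance, it shifts by about −(1 − r) times that imbalance (simulated slopes −0.67, −0.48 and −0.29).

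The SD of a chance imbalance is √(2 × 1.2 / 740) = 0.057 SD units, and 1.96 times that is 0.11. The standard error of the change-score difference is √(2(1 − r)) × √(2 × 1.2 / 629).

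| r (assumed) | Shift at a 1.96-SD imbalance | Standard error |
|---|---|---|
| 0.3 | 0.08 SD | 0.073 SD |
| 0.5 | 0.06 SD | 0.062 SD |
| 0.7 | 0.03 SD | 0.048 SD |

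Even an unusually large imbalance moves the estimate by about one standard error or less.

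**4. Primary outcome.** Adjusting for baseline status multiplies the variance by about 1 − φ².

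| φ (assumed) | Variance factor | Power | Families per arm for 90% power |
|---|---|---|---|
| 0 | 1.00 | 90.0% | 370 |
| 0.3 | 0.91 | 92.5% | 337 |
| 0.4 | 0.84 | 94.3% | 311 |
| 0.5 | 0.75 | 96.3% | 278 |

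Taking a baseline rate of 50%, the SD of chance imbalance is √(2 × 1.2 × 0.25 / 740) = 2.8 points. An imbalance of 1.96 SD (5.6 points) shifts the unadjusted estimate by φ × 5.6, which is 1.7 points at φ = 0.3 and 2.8 points at φ = 0.5.

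**The case against.** **The sentence on change scores fixes only the dependent variable.** A change score regressed on arm and baseline gives the same arm effect as the follow-up value regressed on arm and baseline, and covariate lists are often left to a statistical analysis plan, which is not shown. The equivalence is correct, so the dependent variable need not be replaced. But the article does more than stay silent: the continuous model follows the primary one, whose effect is read from the intercept with no covariate. A baseline covariate cannot simply be added to that model, because the intercept would then mean something else. The stated model itself would have to change.

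**An unadjusted binary primary analysis is legitimate.** It matches the sample-size calculation, which reproduces. This stands. A reader might infer that the trial is underpowered without adjustment; the document's own inputs give 90%.

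**A reader might infer that chance imbalance biases the effect.** It does not. The shift is conditional on the imbalance that happens to occur, and it is part of the sampling error that the standard error already covers.

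**A reader might infer that the change score ignores baseline.** It uses baseline with a fixed coefficient, and for r above 0.5 it is more precise than the follow-up value alone.

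**Baseline goal status is not measured exactly like the outcome.** Cotinine is measured only at years 1 and 2, so baseline tobacco status is self-reported. The count of goals remains a valid pre-randomisation covariate; imperfect measurement reduces the gain.

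**The magnitudes rest on assumed correlations and a borrowed ICC.** This stands. The loss is modest when r is high.

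**Conclusion.** The point holds as a matter of efficiency and robustness. The stated models omit a baseline covariate although the data are collected before randomisation. For the continuous markers, all secondary outcomes, adjustment would cut variance by about 35% to 10% over r = 0.3 to 0.8. For the primary outcome, power would rise from 90% to about 92.5–96% over φ = 0.3 to 0.5. The variance ratio (1 + r)/2 needs only equal variances at the two times. The detectable differences in SD units also need the borrowed ICC and are illustrative. The primary figures use the approximate factor 1 − φ² for baseline goal status.

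The documents do not support calling this a validity error. Both analyses are unbiased under randomisation, and the primary comparison is adequately sized as planned.

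**What to change.** **Continuous markers.** Fit a GEE clustered on family with randomised arm as an explicit term and the participant's own baseline value as a covariate. The dependent variable may be the follow-up value or the change. Read the effect from the arm coefficient, not the intercept.

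**Primary outcome.** Model the follow-up goal indicator itself with an arm term and the number of goals met at baseline (0 to 4), noting that baseline tobacco status is self-reported. Report the standardised risk difference and risk ratio. Keep the unadjusted comparison as a sensitivity analysis. In the same edit, reconcile the outcome definition under Study outcomes, which refers to improvement, with the indicator in the Data analysis plan.

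**Cost.** Analysis wording only: no new measurements, visits or participants. The change should be fixed before the analysts receive the allocation, which the protocol withholds until database lock.

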To compare the cost-utility of the intervention to standard arm management, we propose to calculate an incremental cost/utility ratio [net costs to net utility: costs of intervention – costs of control/utility of intervention – utility of control]. To calculate utility, we will use 12-monthly health utility. The chosen measure of utility will be the closest option to a global measure, the quality adjusted life year (QALY], and is calculated as the sum of mean survival time [life years] x utility scores at 12 and 24 months [25]. Both 12 and 24-month costs per QALY will be reported. If the intervention is successful, the modeled long-term cost-utility of the intervention and usual care will be compared using Markov Chain Monte Carlo estimation techniques, controlling for age, gender, and risk factor prevalence under different plausible scenarios for how these may evolve over time [26]. Then it will be compared to reference points from the literature – e.g., ceiling ratios for costs per QALY that are less than three times gross domestic product (GDP) per capita [27, 28] that are considered cost-effective [29] (India’s 2013 GDP per capita was $3990; threshold: ≤$11,100 per QALY).

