Despite improvements in individual risk factors in multiple risk factor intervention trials, its effectiveness on combined cardiovascular events and mortality are yet to be established [35]. In order to establish the effect of these interventions on cardiovascular morbidity and mortality, large, multi-centric strategic trials are necessary. Given that the power of such studies largely depend on the number of outcome events observed during the study period, they often require a longer follow-up period. Our present study with the median follow-up of just two years is not powered to detect changes in CVD morbidity and mortality. Family based approaches that target both the structural and environmental conditions in which a family lives, and address possible barriers and facilitators of adopting a healthy lifestyle need to be also evaluated for their effectiveness to reduce cardiovascular events and mortality in future.

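### The only within-trial cost-utility result stated is a cost-per-QALY ratio whose denominator may be small against its error; incremental net monetary benefit with a family-clustered interval would be readable where the ratio is not

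*Protocol article*

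**What the plan says.** The cost-utility paragraph of the protocol article's Data analysis plan names the statistic, "we propose to calculate an incremental cost/utility ratio", and gives its formula as the cost difference between arms over the utility difference. The Aim 3 section on cost effectiveness also names an incremental cost utility ratio. The denominator is the between-arm difference in QALYs, which are "calculated as the sum of mean survival time [life years] x utility scores at 12 and 24 months".

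The within-trial commitment carries no condition: "Both 12 and 24-month costs per QALY will be reported".

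A conditional step follows: "If the intervention is successful, the modeled long-term cost-utility of the intervention and usual care will be compared using Markov Chain Monte Carlo estimation techniques". Next comes "Then it will be compared to reference points from the literature", with the example of "ceiling ratios for costs per QALY that are less than three times gross domestic product (GDP) per capita". The figures given are a GDP per capita of $3990 and a threshold of at most $11,100 per QALY.

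The Discussion says the study, with a median follow-up of two years, "is not powered to detect changes in CVD morbidity and mortality".

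**The concern.** A ratio of two estimated differences behaves well only when the denominator is clearly away from zero. Here the survival part of the QALY difference is unlikely to be detectable in two years by the article's own account. What remains is any shift in utility scores. The article gives no expected size for that shift. QALYs are not among the listed secondary outcomes, and the power statement does not name them.

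If the QALY difference can cross zero, two things go wrong with the reported figure:

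- Its sampling distribution splits into large positive and large negative values, so an ordinary interval for the ratio has no useful meaning.
- Its sign stops being informative. A negative ratio can mean cheaper and better, or dearer and worse. A positive ratio can arise from two negative differences, where the sense of a ceiling is reversed.

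At stake is whether the 12- and 24-month economic results can be read at all in direction and precision.

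**Working it through.** **Inputs from the article** (Trial sample size and power; Data analysis plan): 740 participants per arm (370 families of two), 15% loss, ICC 0.20, rates of 45% and 55%, two-sided alpha 0.05, GDP per capita $3990, threshold $11,100.

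**The plan's own figures.** Two proportions of 45% and 55% at 90% power need 524 per arm. The design effect is 1 + (2 − 1) × 0.20 = 1.20, and 524 × 1.20 / 0.85 = 740 per arm. The sample size reproduces. The threshold does not: 3 × 3990 = 11,970. The stated 11,100 is 870 lower (7.3%) and equals 3 × 3700.

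**Effective size for the QALY comparison.** 740 × 0.85 / 1.20 = 524 per arm. The ICC of 0.20 belongs to the binary composite, so using it for QALYs is an assumption. With no clustering the figure would be 740 × 0.85 = 629, and the standard error would shrink only by the factor √(524/629) = 0.91.

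**Assumptions not in the article:** a 24-month QALY SD of 0.10 to 0.30 and a true gain of 0.005 to 0.04.

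**Chance that the estimated gain is zero or negative.** SE = SD × √(2/524) and P = Φ(−gain/SE).

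| QALY SD | SE | gain 0.005 | gain 0.01 | gain 0.02 | gain 0.04 |
|---|---|---|---|---|---|
| 0.10 | 0.0062 | 20.9% | 5.3% | 0.1% | <0.1% |
| 0.20 | 0.0124 | 34.3% | 20.9% | 5.3% | 0.1% |
| 0.30 | 0.0185 | 39.4% | 29.5% | 14.0% | 1.5% |

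**What this does to the ratio.** Take a $50 cost difference (assumed, held fixed), a gain of 0.005 and SD 0.15, so SE = 0.0093:

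- at the true gain: 50 / 0.005 = $10,000 per QALY
- one SE above: 50 / 0.01427 = about $3,500
- one SE below: 50 / (−0.00427) = about −$11,700

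A simulation that also gives cost sampling error (assumed cost difference $100, cost SD $300, QALY SD 0.2, gain 0.005) puts the central 95% of estimated ratios between about −$117,000 and +$122,000. In 34% of simulated trials the ratio lies below $11,100 only because the QALY difference is negative, so the programme is dominated. That share is 21% at a gain of 0.01, 5% at 0.02 and 0.1% at 0.04.

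**Net monetary benefit for the first illustration** (threshold × QALY difference − cost difference):

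- at $11,100: 11,100 × 0.005 − 50 = 5.5, with SE 11,100 × 0.00927 = 103
- at $11,970: 11,970 × 0.005 − 50 = 9.85, with SE 11,970 × 0.00927 = 111

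The estimate is just as imprecise, but it has an ordinary interval and an unambiguous sign. It also moves with the threshold, which is why that figure has to be settled first.

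**The case against.** A reader might infer that the two-year ratio is itself judged against $11,100, and that an exploding ratio could pass. The text does not support this. The comparison with reference points comes after the modelled long-term result, which is undertaken only if the intervention succeeds. What is being compared is slightly ambiguous, but the modelled result is the natural reading. The ceiling is offered as an example benchmark, not as a mechanical rule. A ratio that explodes upward exceeds the ceiling and fails; only a negative one falls numerically below it.

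A reader might also infer that lack of power for cardiovascular events forces the QALY difference towards zero. It does not. QALYs use measured utility as well as survival, and utility can change without events.

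Three further objections have force. An article commonly leaves intervals for ratios and the handling of quadrants to a fuller economic plan, so their absence here is not an error. Every SD, cost and gain above is assumed, and the resulting range of 0.1% to 39% is wide. Net benefit does not make the data more informative.

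What these objections leave standing is that the article does choose a statistic, gives its formula, and commits without condition to reporting it at two time points where its denominator may be weakly estimated.

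**Conclusion.** The point holds as a modest improvement to a stated method. It does not show that the plan reaches a wrong economic conclusion. If the two-year QALY gain is about 0.02 or less, the estimated gain is zero or negative with probability from 0.1% (gain 0.02, SD 0.10) to 39% (gain 0.005, SD 0.30). Towards the upper end of that range the ratio has no stable interval, and its sign does not separate a dominant programme from a dominated one. At a gain of about 0.04 the probability is at most 1.5% and the concern largely goes away. Nothing in the article says which case applies. The results rest on the assumed SDs and gains, and on carrying the composite outcome's ICC over to QALYs.

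Separately, and without any assumption, the threshold of $11,100 does not equal three times the stated $3990.

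**What to change.** 1. Reconcile the threshold with the GDP figure, because net benefit depends on it: 3 × $3990 = $11,970 against the stated $11,100.
2. At 12 and 24 months, report the cost difference, the QALY difference and the incremental net monetary benefit. Give each an interval from a bootstrap that resamples families or from a regression with family clustering.
3. Read any comparison with the threshold, within-trial or modelled, as net benefit above zero.
4. Give the cost-per-QALY ratio only when both differences are positive.

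This uses the same data and needs changed wording plus a little more analysis work. It will not add precision: where the data are weak, the net-benefit interval will be wide and will show it.

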### Cost effectiveness and acceptability analyses (Aim 3)

The intervention costs will include the resource inputs (e.g., personnel salaries, and materials) that are required to deliver the intervention (in total and per participant). Direct and indirect costs incurred by each family will be estimated using questionnaires administered at study visits 0, 12 and 24. Questionnaires will capture direct medical costs, direct non-medical costs (travel), and indirect costs (missed work time, and lost productivity). To estimate the cost-effectiveness (cost per one count decrease in clustering of risk factors), the between trial group difference in intervention delivery and patient direct costs will be divided by the between group difference in clustering of risk factors or cardiovascular risk score: [costs treatment arm – costs standard arm]/[ΣΔ Primary outcome-Treatment arm] – [ΣΔ Primary outcome-usual care arm]. Similarly, incremental cost utility ratio will also be calculated using data from a 12 monthly health utility assessment. Quality adjusted life years (QALY) will be used as the measure of health utility. The acceptability of the interventions will be assessed through qualitative research. Semi-structured FGDs (4-6 each in men and women) and in-depth interviews with FCHW (6 interviews) will be used to gauge the acceptability of the interventions.

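### The cost-effectiveness formula divides by the binary primary outcome although the ratio is named per risk-factor count, and the QALY rule leaves out baseline utility

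*Protocol article*

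**What the plan says.** **Cost-effectiveness ratio** (Protocol article, Cost effectiveness and acceptability analyses, Aim 3). The result is named "cost per one count decrease in clustering of risk factors". The prose says that the cost difference "will be divided by the between group difference in clustering of risk factors or cardiovascular risk score". The formula that follows is "costs treatment arm – costs standard arm]/[ΣΔ Primary outcome-Treatment arm] – [ΣΔ Primary outcome-usual care arm". Under Study outcomes and again in the Data analysis plan, the primary outcome is a status held or not held by each participant: at least three of four risk-factor goals.

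**QALYs** (Protocol article, Data analysis plan). The article states: "To calculate utility, we will use 12-monthly health utility". The QALY "is calculated as the sum of mean survival time [life years] x utility scores at 12 and 24 months". It adds: "Both 12 and 24-month costs per QALY will be reported".

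**Timing of measurements.** In the Aim 2 section: "Study related measurements will be conducted at baseline, one year and two year time-points". For costs, under Aim 3: "Direct and indirect costs incurred by each family will be estimated using questionnaires administered at study visits 0, 12 and 24". No such statement of visits is made for utility.

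**The concern.** The Aim 3 text offers three effect measures for one ratio: a count of risk factors, a risk score and a binary status. They have different units. Improvement lowers the first two and raises the third. A participant who moves from 0 to 2 goals met, or from 3 to 4, changes the count but not the binary status. An analyst following the formula would report a cost per additional participant at goal under the name of a cost per risk factor removed. The choice among the three could also be made after the data are seen.

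The QALY rule names utilities at 12 and 24 months only. Taken with one life year per interval, it treats the 12-month utility as if it had applied since randomisation, and any difference between arms at baseline passes into the QALY difference uncorrected. The intervention is delivered through visits every two months, so a gain that builds up over the first year is plausible. In that case the rule flatters the intervention, most of all in the 12-month ratio that the article commits to reporting.

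The cost-effectiveness results are one of the two inputs to the scalability conclusion; acceptability is the other.

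**Working it through.** The article gives no economic result or utility value to reproduce. Its sample size does reproduce (524 per arm × 1.2 ÷ 0.85 = 740 participants, or 370 families, per arm) and has no bearing here. Only its planning rates, 45% and 55% at three or more goals, are used below.

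**1. Count against binary denominator**

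Assumed for illustration: a cost difference of 50 per participant, and these distributions of goals met (0, 1, 2, 3, 4).

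- Usual care: 0.05, 0.15, 0.35, 0.30, 0.15. At goal 0.30 + 0.15 = 0.45; mean 0.15 + 0.70 + 0.90 + 0.60 = 2.35.
- Intervention A: 0.05, 0.15, 0.25, 0.40, 0.15. At goal 0.55; mean 2.45.
- Intervention B: 0, 0.10, 0.35, 0.30, 0.25. At goal 0.55; mean 2.70.
- Intervention C: 0.05, 0.15, 0.25, 0.20, 0.35. At goal 0.55; mean 2.65.

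| | Difference at goal | Cost per extra participant at goal | Difference in mean count | Cost per count |
|---|---|---|---|---|
| A | 0.10 | 50/0.10 = 500 | 0.10 | 50/0.10 = 500 |
| B | 0.10 | 500 | 0.35 | 50/0.35 = 143 |
| C | 0.10 | 500 | 0.30 | 50/0.30 = 167 |

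The same binary result is compatible with a cost per count anywhere from 143 to 500 in these examples, so one cannot stand in for the other.

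**2. QALY rule against area under the curve**

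Let d12 and d24 be the between-arm utility differences at 12 and 24 months. Assume equal baseline utility, no deaths and straight lines between visits.

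- Rule as written, one life year per interval: d12 at 12 months; d12 + d24 at 24 months.
- Area under the curve: d12/2 at 12 months; d12/2 + (d12 + d24)/2 at 24 months.

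At 12 months the ratio of rule to area is d12/(d12/2) = 2.0 on any such path. At 24 months:

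| d12, d24 | Rule | Area | Ratio |
|---|---|---|---|
| 0.02, 0.02 | 0.04 | 0.03 | 1.33 |
| 0.02, 0.04 | 0.06 | 0.04 | 1.50 |
| 0.04, 0.02 | 0.06 | 0.05 | 1.20 |
| 0.01, 0.05 | 0.06 | 0.035 | 1.71 |

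For a gain that is held after 12 months (first row), cost per QALY is understated by 1 − 1/2.0 = 50% at 12 months and 1 − 1/1.33 = 25% at 24 months.

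**3. Baseline imbalance**

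Take a persisting difference of 0.02 with no treatment effect. The rule gives 0.02 + 0.02 = 0.04 QALY at 24 months. The unadjusted trapezoid also gives 0.04. Only adjustment for baseline utility removes it. With the sign reversed the result is −0.04, so the error can favour either arm.

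**The case against.** The best defence is that this is a condensed article citing a method source for the QALY, and that integration details belong in a fuller economic plan. That would excuse silence, but the article prints a rule and names its two time points. What stands is that 12-monthly assessment neither states nor excludes a month-0 utility, so baseline utility may well be collected and simply not used in the formula.

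It is also fair that the direction of bias is not fixed. If the gain were present from the start and held, the rule would be right and the trapezoid would under-credit it. A gain that peaks before 12 months and then wanes is under-credited by the rule.

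A reader might infer more than the documents support:

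- **The early-closed bracket.** Read literally, the formula subtracts the usual-care change from the ratio. With assumed changes of 0.15 and 0.05 that gives 50/0.15 − 0.05 = 333.28 instead of 50/(0.15 − 0.05) = 500. The prose states the intended division, so this is a typographical slip. If the usual-care change is about zero, as planning on a baseline rate suggests, both forms give 50/0.10 = 500. The missing inner brackets in the cost-utility expression are of the same kind.
- **Three years of utility in two.** Reading survival time as cumulative to each visit would give 1 × u12 + 2 × u24. The text does not say it is cumulative, and one life year per interval is the natural reading.
- **Sums that depend on arm size.** The summation sign is undefined, and costs are taken both in total and per participant, so a mismatch of scale is not shown.
- **A wrong verdict against the GDP threshold.** That comparison is attached to the modelled long-term ratio, not clearly to the within-trial one.

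**Conclusion.** The point holds for two stated rules. First, the printed cost-effectiveness formula does not yield the ratio it is named for: a count decrease is named, a risk score is allowed, and a binary outcome is used. This follows from the text alone; only the 143 to 500 range rests on assumed costs and distributions.

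Second, the QALY rule, followed as written, credits the 12-month utility difference to the whole first year and does not correct for baseline imbalance. It still produces a cost per QALY, but a potentially biased one. The overstatement of the QALY gain, 2.0 times at 12 months and 1.33 times at 24, assumes an equal start, linear build-up to 12 months and a held gain. Other paths give less or more, and a chance imbalance can go either way. An unconditional claim of bias towards the intervention is not supported.

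Both rules should be corrected before the economic analysis. The Aim 2 effectiveness result does not depend on them.

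**What to change.** **Cost-effectiveness ratio.** Define it as (mean cost per participant, intervention minus usual care) ÷ (between-arm difference in mean number of risk factors off goal at 24 months, adjusted for the baseline count), with the whole difference inside the denominator and its sign set so that a decrease counts as benefit. Report cost per additional participant at three or more goals as a separately labelled ratio, and likewise cost per unit of risk score if that is kept.

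**QALYs.** Compute for each participant the trapezoidal area (u0 + u12)/2 × 1 year + (u12 + u24)/2 × 1 year, with utility zero after death. Use the first term alone for the 12-month ratio. Adjust the between-arm difference for baseline utility.

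**Check first** that the 12-monthly utility assessment includes the baseline visit. The general measurement schedule and the cost questionnaires do include it, but the article does not say so for utility.

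**Cost.** If baseline utility is collected, this is analysis work only. If it is not, the QALY change requires adding that assessment. Cost per QALY may look less favourable, and several labelled ratios replace one.
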